## APPENDIX 6: GRADING OF GENITAL REACTIONS

| PARAMETER                                                            | Grade 1                                                           | Grade 2                                                                                                                          | Grade 3                                                                          | Grade 4                          |
|----------------------------------------------------------------------|-------------------------------------------------------------------|----------------------------------------------------------------------------------------------------------------------------------|----------------------------------------------------------------------------------|----------------------------------|
|                                                                      | Mild                                                              | Moderate                                                                                                                         | Severe                                                                           | Life-threatening                 |
| Genital discomfort (including dysuria, pruritis, dyspareunia) | Easily tolerated                                                  | Aware of symptoms at most times
But not preventing daily activities. Able to control symptoms with medication from pharmacies | Unable to control symptoms such that cannot undertake essential daily activities | Hospitalisation for pain control |
| Non-menstrual bleeding                                        | Light (spotting or brown discharge) $\leq 7$ days                 | Light (spotting or brown discharge) $> 7$ days
Or
Heavy (bleeding like menses) $\leq 4$ days                               | Heavy (bleeding like menses) $> 4$ days
Or
Profuse of any duration         | Hospitalisation for transfusion  |
| Signs of epithelial disruption (sores or ulcers)              | $\leq 1$ swab-tip*                                                | $> 1 \leq 4$ swab-tips*                                                                                                          | $> 4$ swab-tips*                                                                 | Hospitalisation                  |
| Erythema (redness)                                            | Local/diffuse mild redness
or
Local moderate/severe redness | Diffuse moderate/severe redness
With genital discomfort symptoms that are easily tolerated                                    | Diffuse moderate/severe redness with Grade 2 genital discomfort symptoms         | Hospitalisation                  |
| Oedema                                                        |                                                                   | Oedema without sloughing of the epithelial cells                                                                                 | Oedema with sloughing of the epithelial cells                                    |                                  |

\*swab-tip is 5 x 10mm

## APPENDIX 7: GRADING OF CLINICAL AND LABORATORY ADVERSE EVENTS

Based on systems in use at the MRC CTU and NIH Division of AIDS (unless stated otherwise).

### Abbreviations:

|                |                            |     |                       |
|----------------|----------------------------|-----|-----------------------|
| ULN            | Upper Limit of Normal      | LLN | Lower Limit of Normal |
| R x | Therapy                    | Req | Required              |
| Mod            | Moderate                   | IV  | Intravenous           |
| ADL            | Activities of Daily Living | Dec | Decreased             |
| OTC            | Over the counter           |     |                       |

The tables below define clinically significant abnormal pathology results which are classed as AEs. Any results that are outside of the normal range for the laboratory at York Hospital but do not meet the criteria for being classed as an AE will not be classed as such. For events or results that are not specified in the tables, a decision will be made by the CI or a trial physician, as delegated by the CI, as to whether the result is clinically significant. Only those events or results that are deemed clinically significant will be classed as AEs.

For clinical events not specified in the tables below the following grading should be applied:

- *Grade 1 (mild)*: Awareness of sign or symptom but tolerated with minimal or no interference with ADLs. Transient (< 48 hours). May be relieved by OTC medication but no other medical intervention required.
- *Grade 2 (moderate)*: Notable symptoms resulting in greater than minimal interference with ADLs. No or minimal medical intervention required.
- *Grade 3 (severe)*: symptoms causing significant incapacity resulting in bed rest or activity reduced by >50% of usual level and/or unable to work. Medical intervention required.
- *Grade 4 (extreme/life-threatening)*: Significant medical intervention/therapy required; hospitalization required to prevent permanent impairment or death.

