| Myalgia                  | 0                                     | 0                                     | 5/14                          | 3/10                                |
| Arthralgia               | 0                                     | 0                                     | 4/14                          | 1/10                                |
| Skin rash                | 0                                     | 0                                     | 1/14                          | 1/10                                |

The results of these trials are detailed in the Investigator's Brochure. In summary, no serious adverse events (SAEs) or thrombotic complications were reported, and very few possible adverse drug reactions (ADRs) were observed. The most common adverse events reported were myalgia, arthralgia, and skin rash. These were generally mild and resolved during or shortly after cessation of dosing. Direct evidence was obtained that these monoclonal antibodies contributed to the temporary containment of HIV-1 replication in infected humans.

Further analyses and experiments in relation to these clinical trials were recently reported, which investigated the possibility of autoreactivity and possible thromboembolic disorders associated with C4E10 and C2F5. During trial 4 (as above table) the study design was modified to collect prospective data from the last four high-dose patients. Very mild (<1.25 x ULN) prolongation of the APTT 30 minutes post-infusion was observed which rapidly remitted, and there was no effect on the PT. In vitro experiments indicated that the effect on coagulation profile was mediated by 4E10. Further analyses indicated that C4E10, but not C2F5, also showed low-level cross-reactivity with cardiolipin, and that infusion of C4E10 resulted in transient low anti-cardiolipin antibody titres. It was concluded that there was little evidence that the monoclonal antibodies conferred an increased risk of thrombosis, but that monitoring of both coagulation parameters and anti-phospholipid antibodies should be carried out in any further clinical trials.

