### **6.2 Exclusion criteria**

- Untreated syphilis, gonorrhoea, trichomonas, chlamydia, vaginal candidosis or bacterial vaginosis
- Clinically significant (out of the normal range and deemed clinically significant by the CI or study physician) haematological, biochemical, immunological or coagulation assay abnormalities on screening
- HIV infection, anti-HCV antibody positive, HbsAg positive
- Abnormal findings on pelvic examination, deemed clinically significant by the CI or study physician
- History of coagulation or thrombotic disorders
- Significant current general medical illness
- Irregular menstrual bleeding likely to cause vaginal bleeding during the dosing period as judged by the CI or study physician
- Current participation, or participation within the last 2 months in another clinical trial
- Treatment for cervical intraepithelial neoplasia (CIN) or other gynaecological instrumentation of the cervix within the past 3 months
- Pregnant, within 12 weeks postpartum, or breast feeding
- Unlikely to comply with protocol
- Have any condition which, in the opinion of the CI or study physician, might interfere with the evaluation of the study objectives

- Unable to fluently read and speak English to a level adequate for the full comprehension of procedures required in participation and consent

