#### **6.4.3 Screen failures**

If the HIV/Syphilis, Hepatitis B or C tests are positive, the participant is not eligible for the trial and will be immediately considered a screen failure. The participant will be given the result (independent of his/her partner unless otherwise specified by the participant) by an appropriate Clinical Investigator and provided with the opportunity for same day referral to a GU physician.

If the pregnancy test is positive, the participant is not eligible for the trial and will be immediately considered a screen failure. The participant will be given the result by an appropriate Clinical Investigator and provided with the opportunity for referral to Family Planning services if appropriate.

If the results for STIs are positive for Chlamydia, gonorrhoea, Trichomonas vaginalis, vaginal candidosis or bacterial vaginosis the participant will be offered the opportunity to be referred to GUM services within 48 hours of results or given the choice to be treated and managed

by a study physician.. If the relevant infection is properly treated with acceptable contact tracing parameters, then the participant will be offered the opportunity to continue with their participation in the study after at least one further menstrual cycle has elapsed. In this case the participant will be assigned a different SID upon re-entry into the trial and the screening visit will be repeated.

If any of the routine screening blood test results are outside normal range (as defined by current York Pathology laboratory ranges) and are deemed to be clinically significant by the CI (or study physician in accordance with the delegation log) the participant will be asked for permission to inform her GP. Similarly, if any abnormalities are detected on genital or physical examination and are deemed to be clinically significant by the CI (or a study physician in accordance with the delegation log) permission to inform the participant's GP or another appropriate physician will be sought.

Depending on the abnormality, its natural history and clinical significance, the participant may be enrolled into the dosing stage of the trial, undergo further investigations, or be considered a screen failure, as determined by the CI (or study physician according to the delegation log). The participant may be assigned a different SID if enrolled after further investigation and/or resolving of the abnormal finding, in which case the screening visit will be repeated.

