| Laboratory parameters                                     | Pregnancy test a           | X               |                             | x                                   |                                       |                                        |      |              |       |                                         |                                         |                 | x    |
|                                                           | Urinalysis a               | x               |                             |                                     |                                       |                                        |      |              |       |                                         |                                         |                 |      |
|                                                           | Biochemistry b             | x               |                             |                                     |                                       |                                        |      |              |       | x                                       |                                         |                 | x    |
|                                                           | Haematology c              | x               |                             |                                     |                                       |                                        |      |              |       | x                                       |                                         |                 | x    |
|                                                           | Hepatitis B/C serology                | x               |                             |                                     |                                       |                                        |      |              |       |                                         |                                         |                 |      |
|                                                           | APTT/aCL d                 | x               |                             | x                                   |                                       | x                                      |      |              |       | x                                       |                                         |                 | x    |

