| Adverse Event (AE):                   | 
Any untoward medical occurrence in a subject to whom a medicinal product (in this case, study gel) has been administered, including occurrences which are not necessarily caused by or related to that product.
 
An AE can therefore be any unfavourable and unintended sign (including an abnormal laboratory finding), symptom, or disease temporally associated with the use of an investigational medicinal product (IMP), whether or not considered related to the IMP.
 
Note: The above definition has been taken from the Medicines for Human Use (Clinical Trials) Regulations 2004. However for the avoidance of doubt, in line with the North and East Yorkshire R and D Alliance Research Related Adverse Event Reporting Procedures, all AEs will be collected for all trial subjects from the time of their enrolment into the study, whether an IMP has been administered to the subject or not.
 |
| Solicited Genital Adverse Event (AE): | One of the specified adverse events that will be systematically solicited during visits. These events are listed by grade in Appendix 6.                                                                                                                                                                                                                                                                                                                                                                                                                                                                                                                                                                                                                                                                                                                                                                                                               |

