- Number of grade 3 or above other clinical or laboratory adverse (Appendix 7) events confirmed at examination or on repeat testing respectively during the dosing or follow up period
- All adverse events (irrespective of assigned relationship to study gel)
- All adverse events classed as possibly or probably treatment-related.

Details of sub-study analyses are provided in section 12.

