## IMMUNOLOGY

|                             |                  |                   |                  |             |
|-----------------------------|------------------|-------------------|------------------|-------------|
| C Reactive Protein          | 15 - 50mg/L      | >50 – 150 mg/L    | >150 – 250 mg/L  | > 250 mg/L  |
| Anti-cardiolipin antibodies |                  |                   |                  |             |
| IgG                         | > 1 - 1.25 x ULN | > 1.25- 1.5 x ULN | >1.5 – 3.0 x ULN | > 3.0 X ULN |

Note: The above AE criteria for CRP and anti-cardiolipin antibodies have been devised by the CI as no DAIDS/MRC CTU gradings exist for these parameters.

In contrast to IgG antiphospholipid antibodies, elevated levels of IgM anticardiolipin antibodies are significantly less indicative of possible antiphospholipid syndrome/SLE and have not been induced by C4E10, C2F5 or C2G12 in previous studies. They will therefore not considered an adverse event unless accompanied by raised IgG, coagulation parameter abnormalities or clinical features suggestive of antiphospholipid syndrome/SLE.

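### Appendix 7 classes APTT, creatinine and IgG anticardiolipin values above 1 x ULN as adverse events without reference to the pre-dose value, so a stable pre-existing value can count as an event in the arm comparisons

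*Protocol*

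**What the plan says.** **After entry.** Appendix 7 introduces its laboratory tables with: "The tables below define clinically significant abnormal pathology results which are classed as AEs". An out-of-range result that does not reach a table threshold is not an AE. For APTT, creatinine and IgG anticardiolipin the lowest threshold is the upper limit of normal itself. The anticardiolipin and CRP scales "have been devised by the CI as no DAIDS/MRC CTU gradings exist for these parameters"; most of the rest follow existing grading systems.

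**At entry.** Section 6.2 excludes a laboratory abnormality only if it is "out of the normal range and deemed clinically significant by the CI or study physician". Section 6.4.3 adds that, depending on the abnormality, "the participant may be enrolled into the dosing stage of the trial".

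**Collection.** Under 9.1, "all AEs will be collected for all trial subjects from the time of their enrolment into the study", whether or not gel has been given.

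**Analysis.** Section 10.2.2 compares event counts in the three arms by negative binomial regression. One comparison is "All adverse events (irrespective of assigned relationship to study gel"). Another takes AEs judged possibly or probably related. The count of grade 3 or above laboratory events requires confirmation on repeat testing; the other two do not.

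**Other uses of the grades.** Discontinuation of dosing (9.4.2) and the three-woman halt (9.5) also run on grade 3 or above. Neither mentions a pre-dose value or a repeat test.

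**The concern.** The same result is treated in two ways. At screening, a value slightly above ULN is a matter for clinical judgement. After entry it is clinically significant by definition and an AE. Because no laboratory row refers to the pre-dose value, a woman who enters slightly above ULN and stays there produces events that say nothing about the gel. The protocol does grade by change elsewhere: the hypertension row uses a rise in diastolic pressure.

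The case that matters most is IgG anticardiolipin, where grade 3 starts above 1.5 x ULN. A repeat test shows that a value persists, not that it is new, so a stable pre-existing value could become a confirmed grade 3 event.

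Section 3.4 reports the recommendation that coagulation parameters and anti-phospholipid antibodies be monitored in further trials. The stated comparisons handle these only as counts of threshold crossings. Such counts take in unchanged values and ignore any rise that stays below ULN.

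**Working it through.** The protocol gives no event rate or power figure for safety, so there is nothing of its own to reproduce.

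**1. Thresholds (Appendix 7, in multiples of ULN)**

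| Parameter | Grade 1 above | Grade 3 above | Pre-dose reference |
|---|---|---|---|
| APTT | 1 | 2.33 | none |
| Creatinine | 1.0 | 3.0 | none |
| IgG anticardiolipin | 1 | 1.5 | none |

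Consistency check: section 3.4 says "Very mild (<1.25 x ULN) prolongation of the APTT 30 minutes post-infusion was observed". That falls in grade 1 or below, as section 13.4 also says. It can therefore never reach the grade 3 count.

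**2. Expected crossings with no gel effect**

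Table 7-1 is read as giving APTT and anticardiolipin at visits 1 and 2 before the gel and three times after it, and biochemistry once before and twice after. That creatinine is part of the U&Es is an assumption. Post-dose values: 3 + 3 + 2 = 8 per woman, and 30 x 8 = 240 in all. If a share p of healthy values lies above ULN (assumed):
- p = 1%: 240 x 0.01 = 2.4
- p = 2.5%: 240 x 0.025 = 6.0
- p = 5%: 240 x 0.05 = 12.0

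**3. Pre-existing values versus chance crossings**

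Model (assumed): value = woman effect (variance r) + visit noise (variance 1 - r), with ULN at the 97.5th percentile.

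| | r = 0.5 | r = 0.7 | r = 0.85 |
|---|---|---|---|
| Above ULN at screening on APTT or anticardiolipin: at least one of three post-dose values above ULN | 40% | 58% | 74% |
| All three parameters normal at screening: at least one post-dose event on any | 14% | 11% | 8% |
| The same women, counting only a grade above the highest pre-dose grade | 12.7% | 9.4% | 6.2% |

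The first row is the pre-existing problem. The second, about one woman per arm of 10, is mostly ordinary variation around a cut-off, and the worsening rule removes little of it.

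For one parameter with two pre-dose and three post-dose values, and no filter at screening, the rule lowers the share of women with an event from 6.3 to 4.6% (r = 0.5), 5.4 to 3.2% (r = 0.7) and 4.2 to 1.6% (r = 0.9).

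**4. Anticardiolipin near grade 3**

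Take a woman steady at 1.4 x ULN, with an assumed assay CV of 10% or 15%.
- One reading above 1.5: 1 - Φ(0.1/0.14) = 0.238, or 1 - Φ(0.1/0.21) = 0.317.
- At least one of three readings: 1 - (1 - 0.238)³ = 0.557, or 1 - (1 - 0.317)³ = 0.681.
- With an independent repeat also above 1.5: 1 - (1 - 0.238²)³ = 0.16, or 1 - (1 - 0.317²)³ = 0.27.

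The last line applies to the endpoint in 10.2.2. The line before it applies where no repeat is mentioned (9.4.2, 9.5).

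**5. Visibility of a small shift**

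Assume a sustained APTT shift at the two post-dose visits during and just after dosing, with 10 women against 10. Compare women with any value above ULN (Fisher's exact test) with the mean post-dose value adjusted for the mean pre-dose value.
- Shift of 1 SD: about 3 to 6% power by counting, 88 to 100% by the adjusted comparison.
- Shift of 0.5 SD: under 1% by counting; 36%, 50% and about 76% by the adjusted comparison at r = 0.5, 0.7 and 0.85.

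Fisher's test on one parameter stands in for the planned negative binomial regression. That regression mixes these crossings with all other AEs.

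**The case against.** **The analysis plan may deal with this.** Section 10.2 refers to a detailed SAP that is not at hand, and a worsening rule or an analysis of change could sit there. So the absence of such an analysis is not itself a finding. What stands is the text the protocol does fix: Appendix 7 decides what is an AE, and 10.2.2 names the counts.

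**A known C4E10 effect is lost.** A reader might infer this, but the documents do not support it. The APTT prolongation was seen 30 minutes after gram-dose infusion and remitted rapidly. Section 13.4 puts the dose here at about 1/50 of that in earlier studies, and macaque serum levels were in the nanogram range. The effect may not arise at all, or may be gone by the sampling visits. A rise that does cross ULN is still recorded as grade 1 and can enter the all-AE and related-AE counts. The shifts in step 5 are illustrations, not predictions.

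**The safety comparison is biased.** It is not. Chance and pre-existing values should fall evenly over arms in a randomised, double-blind trial, and causality assessment may remove unchanged values from the related-AE count.

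**Spurious grade 3 events are likely.** They are not. A woman at 1.4 x ULN is already grade 2 on the anticardiolipin scale. Section 6.2 excludes clinically significant immunological abnormalities, and Appendix 7 itself links raised IgG to possible antiphospholipid syndrome. The discretion in 6.4.3 makes her enrolment possible, no more. APTT grade 3, above 2.33 x ULN, is practically unaffected.

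**Conclusion.** The point holds in limited form. The protocol classes any APTT, creatinine or IgG anticardiolipin value above ULN as a clinically significant AE without looking at the pre-dose value, while entry leaves significance to judgement. A stable pre-existing value can therefore count in the all-AE comparison. A persistent IgG anticardiolipin value above 1.5 x ULN could be a confirmed grade 3 event, although such a woman is unlikely to be enrolled.

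The consequence is non-differential noise, with a small coagulation or anticardiolipin shift hard to see in the counts. Most threshold crossings in women normal at screening are ordinary variation, which the worsening rule does not cure. The continuous comparison is what improves sensitivity.

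The sizes rest on assumptions outside the protocol: the share of healthy values above ULN, the between-woman variance share, the assay CV and a sustained shift. This is a cheap improvement worth making, not a threat to the trial's primary pharmacokinetic aim.

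**What to change.** 1. In 10.2.2, count a post-dose laboratory result in the arm comparisons only if its grade is higher than the woman's highest pre-dose grade. Apply this to the grade 3 or above laboratory count as well, in addition to the repeat test.
2. Compare post-dose APTT and IgG anticardiolipin as continuous values adjusted for the pre-dose value, each active arm against placebo, with 95% confidence intervals.
3. Reconcile 6.2, 6.4.3, 9.4.2, 9.5 and Appendix 7 on how a pre-existing laboratory value is treated. The clinical handling is for the sponsor.

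Cost: wording in 10.2.2 and Appendix 7 and one added analysis, with no new samples. Confirm from Table 7-1 that the visit 2 sample is drawn before the gel; otherwise visit 1 alone is the pre-dose value. The downside is that an abnormality which persists without worsening is listed as a baseline finding and not counted as an event.
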